### Harms

The risks arising from participation are considered very low. The interventions proposed are those already offered to patients in specialist centres throughout the UK and internationally. The only difference conferred by participation is that these interventions will be randomly allocated and more carefully assessed. All interventions are safe. For instance, the only invasive tests (INVEST) have been performed daily in most specialist centres for up to 30 years without any recorded complication (experience of the lead centre is more than 122,000 patients). A small ionising radiation dose is required for two tests. All devices used in the study are CE-marked and will be used in accordance with manufacturer’s instructions and intended uses.

A number of questionnaires contain personal questions about bowel problems and the effect of these on quality of life and psycho-behavioural functioning; however, all have been used in studies of similar patients previously.

The benefits of participation are that patients will receive a very high standard of monitored care as a consequence of the detailed protocol. In some instances (geographically), patients may receive interventions for which they did not previously have access.

There are minimal safety considerations attributable to the interventions. Patients allocated to INVEST-guided therapy will undergo two radiological procedures (whole gut transit study and evacuation proctography) using ionising radiation as outlined above. The combined dose of these procedures (approximately 1.2 mSv) is equivalent to less than 7 months’ annual background radiation dose from living in the UK. Further, these investigations would be carried out in routine clinical practice in many centres for patients at the same point as recruitment to this study. There are rare reports of local irritation or discomfort subsequent to manometry and very rare reports of rectal perforation after manometry [79], but only in the presence of prior radiotherapy and surgery.

As no medicinal products are being administered as part of the trial and all trial interventions are as per the standard care provided within the NHS for chronic constipation, unrelated AEs will not be recorded on the CRF. Causality will be at the discretion of the health care provider. Serious adverse events (SAEs) will be recorded on the CRF and in the medical notes to enable assessment and reporting in line with sponsor and regulatory requirements.

Trial participants will be advised to seek medical support from their family physician for any unrelated signs, symptoms or disease or aggravation of underlying symptoms.

SAEs that are considered to be ‘related’ and ‘unexpected’ are to be reported to the chief investigator and sponsor within 24 h of the site learning of the event and by the coordinating team to the REC within 15 days in line with the required time frame.

The following SAEs are expected to occur rarely in this patient population and will not be reported:Hospital admission for exacerbation of constipation symptoms including impactionHospital admission for unrelated elective surgical procedures or accidental injury

In the event that participants suffer harm during the research study, and this is due to someone’s negligence, then participants may have grounds for legal action against the sponsor Queen Mary University of London. Insurance and indemnity is provided by the sponsor to cover such claims.

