##### Visits 2–5: interventions

Participants randomised to treatment without INVEST will undergo four sessions of standardised therapy (HT or HTBF) (Tables 1 and 2). Those randomised to INVEST will have additional radio-physiological investigations (Table 3) prior to being stratified to receive either HT or HTBF. A review of all related AEs and changes in confounding medications will be conducted at each intervention visit.

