##### Visits 6–8: follow-up outcome assessments (3, 6 and 12 months)

The standardised outcome questionnaires booklet will be completed and the 2-week Bowel Diary and Patient Journal completed and returned, including a review of all related AEs and changes in confounding medications. In order to maximise completeness of data collected, the 3- and 6-month follow-up visits will be conducted face to face wherever possible. Follow-up at 12 months can, however, be conducted by telephone. The 6-month time point at which the primary outcome is recorded will coincide with the end of a protocol-imposed ‘quarantine’ period during which a participant’s response to therapy will remain unconfounded by treatment progression.

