#### Blinding

Patients and clinicians are necessarily aware of both INVEST and treatment allocations after randomisation. The primary outcome and several other outcomes are self-reported. All those involved in developing the statistical analysis plan will be blinded to allocation status until the plan is signed off, and no analyses of outcomes will be undertaken until that is done. To minimise observer bias, a blinded researcher will collect outcome data. If a blinded researcher is unavailable, the primary outcome questionnaire will be completed by the participant without assistance and secured in an envelope.

Statisticians performing the analysis will remain blinded.

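### Non-serious adverse events reach the CRF only if a provider who knows the allocation calls them related, so any comparison of adverse events between arms is open to differential ascertainment

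*Protocol article*

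**What the plan says.** The recording rule is in the Harms section of the protocol article: "unrelated AEs will not be recorded on the CRF. Causality will be at the discretion of the health care provider". The reasons given are that no medicinal product is administered and that the interventions are standard NHS care.

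The visit schedule applies the same restriction. Under Visits 2–5: "A review of all related AEs and changes in confounding medications will be conducted at each intervention visit". Under Visits 6–8, the follow-up booklet and diary are completed, "including a review of all related AEs and changes in confounding medications".

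On who knows the arm, the Blinding section says: "Patients and clinicians are necessarily aware of both INVEST and treatment allocations after randomisation". It also says: "To minimise observer bias, a blinded researcher will collect outcome data". It does not mention causality assessment.

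Serious events are handled separately. The Harms section says: "Serious adverse events (SAEs) will be recorded on the CRF and in the medical notes to enable assessment and reporting", with no condition on relatedness. Two kinds of admission are then exempted (constipation exacerbation including impaction, and unrelated elective surgery or accidental injury): "The following SAEs are expected to occur rarely in this patient population and will not be reported". That exemption is worded as one from reporting and does not mention the CRF.

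For other complaints: "Trial participants will be advised to seek medical support from their family physician for any unrelated signs, symptoms or disease or aggravation of underlying symptoms".

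**The concern.** Relatedness is normally an attribute of a recorded event. Here, for non-serious events, it decides whether the event is recorded at all, and the person deciding knows the arm. No attribution criteria, adjudication or solicited list is described in the article.

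The arms give that person different prompts. HT (Table 1) involves no rectal instrument, and the therapist may not use digital rectal examination for training. HTBF adds a manometry catheter and balloon at each session (Table 2). Everyone in INVEST has anorectal manometry, balloon tests and proctography before therapy (Table 3). The only procedural harms named in the Harms section, local irritation or discomfort and rectal perforation, are linked to manometry. The same anorectal complaint could plausibly be called related after instrumentation and unrelated without it.

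The Background weighs possible guidance of treatment against the invasive nature of some tests, and the Discussion hopes to inform whether invasive tests are warranted and whether biofeedback adds benefit. Readers of the results are likely to look at adverse events by arm. An analysis plan cannot correct a filter applied before the data reach the database.

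**Working it through.** **Inputs from the documents.** The recording rule (Harms); related events only at planned reviews (Visits 2–5, Visits 6–8); clinicians aware of allocation (Blinding); instrumentation in HTBF and INVEST but not HT (Tables 1–3); 147 participants each in HT and HTBF (Sample size: 132 / 0.9 = 146.7, rounded up to 147).

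**Inputs that the documents do not give.** Event rates and the probability that an event is called related, by arm. The values below are assumptions. The plan has no adverse-event figure to reproduce.

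**Formula.** Let p be the true rate of a non-serious event and a the probability that the provider calls it related. Then:

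- recorded rate = p × a
- recorded ratio (HTBF / HT) = (p_HTBF / p_HT) × (a_HTBF / a_HT)

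With equal true rates this reduces to a_HTBF / a_HT, whatever p is.

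**Range, with an assumed true rate of 10% in both arms and 147 per arm:**

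| a_HTBF | a_HT | Recorded rates | Expected events | Recorded ratio |
|---|---|---|---|---|
| 0.5 | 0.5 | 5% v 5% | 7.4 v 7.4 | 1.0 |
| 0.6 | 0.4 | 6% v 4% | 8.8 v 5.9 | 1.5 |
| 0.8 | 0.4 | 8% v 4% | 11.8 v 5.9 | 2.0 |
| 0.9 | 0.1 | 9% v 1% | 13.2 v 1.5 | 9.0 |

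For example, in the third row, 147 × 0.10 × 0.8 = 11.8 and 147 × 0.10 × 0.4 = 5.9. If the recorded proportions were tested at the 5% level (normal approximation), the chance of a spurious significant excess in HTBF would be about 12% in the second row and 30% in the third. These chances depend on the assumed 10%: at a true rate of 5% they are about 8% and 17%.

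**The error can run the other way.** If providers attribute less readily to biofeedback, say 0.4 in HTBF and 0.8 in HT, a true ratio of 2.0 would be recorded as 2.0 × (0.4 / 0.8) = 1.0.

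**With every occurrence recorded,** a = 1 in each arm and the recorded ratio equals the true ratio, so far as events are reported equally. Participants also know their allocation, so a common question reduces unequal reporting but cannot abolish it.

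**The case against.** The strongest reply is that the rule is a proportionate choice for a low-risk trial of standard care, and that the article plans no comparison for it to damage. Adverse events are not among the objectives, the clinical endpoints or the statistical methods. This stands in part. It limits the point to any adverse-event comparison that is reported, and it argues for a short list over full recording. It does not justify a filter that can operate differently by arm.

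Second, differential attribution is not shown. HT includes stopping laxatives, rescue suppositories, pushing manoeuvres, splinting and, for some, pelvic floor exercises, to which a provider could attribute pain or bleeding. HTBF contains all of HT. This stands: the absence of an instrument does not settle attribution, and the direction stays open.

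Third, dropped events are not wholly lost. The patient journal captures health contacts and concurrent medication in every arm, PAC-SYM captures symptoms, and resource use includes treatment sequelae. These are a partial backstop, not an event log.

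Some stronger readings are tempting, but the documents do not support them:

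- *That only related events of any kind are recorded.* Serious events go on the CRF with no relatedness condition.
- *That the comparison is biased by construction, with a large excess in HTBF.* Bias arises only if attribution differs by arm, and any multiple simply restates the assumed probabilities.
- *That the treating therapist makes every causality call.* The text says only health care provider.
- *That follow-up reviews break the assessor's blinding.* The Blinding section gives the blinded researcher outcome data, and Visits 6–8 does not say who reviews adverse events. The primary outcome is in any case self-reported by a participant who knows the arm.
- *That events from the INVEST tests go uncollected.* No review is specified at the tests themselves, but the first therapy session follows them and includes one, and participants withdrawn from treatment remain in follow-up unless they decline it.

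**Conclusion.** The point holds for non-serious events. Their entry on the CRF depends on a causality judgement by someone who knows the allocation, in a trial whose arms differ in rectal instrumentation. Recorded counts by arm are therefore open to differential ascertainment, and later analysis could not fully repair this.

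Neither direction nor size can be derived from the documents. With equal true rates, the recorded ratio equals the ratio of attribution probabilities. Across the assumed values above it runs from 1.0 (equal attribution) to 9.0 (an extreme case), and the reverse direction is equally possible. The primary outcome, the sample size and the recording of serious events are unaffected. This is a worthwhile, inexpensive improvement to data collection. It does not threaten the trial's main conclusions.

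**What to change.** At the reviews already planned under Visits 2–5 and Visits 6–8:

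1. Ask participants in all three arms the same question about a short fixed list of anorectal and abdominal events (for example rectal bleeding, anorectal pain, abdominal pain).
2. In INVEST, have the first review cover any such event since the tests.
3. Record every listed occurrence regardless of attribution, and enter relatedness as a separate field. Other unrelated non-serious events can stay off the CRF, which keeps the low-risk rationale.
4. At visits 6–8, complete the outcome booklet before the adverse-event review, so that the order of tasks cannot affect the outcome data.

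Serious events need no change on this point. The cost is a revision of the CRF and visit checklist and somewhat more adverse-event entries. No visit is added.

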#### Group 1: habit training (HT)

Habit training will be provided by trained specialists (e.g. nurses or physiotherapists) with clinical experience, who have undertaken an additional study-specific standard 1-day training session. A standardised approach and intervention will be provided via use of an intervention manual; at least one random observation visit will be performed early in the study by lead research nurses for quality control.

The course of therapy will include a minimum of three, maximum of four sessions (45–60 min each session). This will use a standardised session proforma with an interval tolerance of every 3–5 weeks. The first and last session will always be face to face. Sessions will be delivered by the same therapist if at all possible and tailored to participants’ individual needs. Each recruiting site will provide sufficient resource to cover visits in therapist absence or holiday. Participants will receive the interventions in Table 1 which are covered in a booklet given to each participant. The therapist is prohibited from using digital rectal examination to train manoeuvres and will complete relevant sections in the participant booklet advising on individual instructions.

**Table 1 Tab1:** Interventions for habit training (HT – group 1)

a. Provision of a written information leaflet covering normal bowel function; causes of constipation; diet and fluid advice; getting into a good bowel habit
b. Review of written information using locally available teaching tools such as models or diagrams
c. Advice to stop all laxatives including drugs which have a laxative effect or over the counter herbal teas that contain strong purgatives. One or two glycerin suppositories are permitted as rescue if no stool is passed for 3 days. No use of irrigation devices or enemas
d. Encouragement to follow a daily routine: sit on the toilet for 20–30 min after first meal and/or hot drinks (sooner if urge felt)
e. Advice to attempt defaecation after meals or when urge is felt, but no more than 3 times per day
f. Advice to sit on toilet with knees bent to 45° position with feet elevated on stool or equivalent; abdominal brace and breathe while performing anal relaxation
g. Advice only to attempt to push for 5–10 min maximum
h. Teaching on defaecation manoeuvres, taught while the patient is positioned sitting on chair with verbal coaching to breathe while pushing
i. Strong discouragement from multiple attempts and prolonged straining

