#### Laxative use

All participants will be asked to discontinue laxative use at the first intervention visit and to refrain from using laxatives throughout the trial, as is standard UK practice in specialist biofeedback services. However, it is inevitable that participants will seek recourse to laxatives and other dietary supplements during the course of the programme. Experience shows that complete prohibition can lead to unreported laxative use, which might confound findings. Although we will strongly discourage ad libitum medication usage and specify a defined breakthrough regimen, we will record co-treatment with sufficient fidelity and integrity to enable use as covariates in analyses using a specific journal for this purpose (within the patient journal: see ‘Study Outcome Measures’). A concomitant medications list, including a shortlist of contributory or confounding medications, will be used to filter on data entry.

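### The rule that admissions for worsening constipation or impaction are not reported as SAEs has no relatedness condition, although every arm stops laxatives, and it conflicts with the stated purpose of recording SAEs

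*Protocol article*

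**What the plan says.** All references are to the protocol article.

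- **Harms, exemption.** "The following SAEs are expected to occur rarely in this patient population and will not be reported". Two items follow. The first is admission for worsening constipation, including impaction. The second is admission for elective surgery or accidental injury. The word unrelated appears in the second item only.
- **Harms, expedited route.** SAEs that are both related and unexpected "are to be reported to the chief investigator and sponsor within 24 h of the site learning of the event", and the coordinating team passes them to the ethics committee within 15 days.
- **Harms, recording.** "Serious adverse events (SAEs) will be recorded on the CRF and in the medical notes to enable assessment and reporting". No class of SAE is excepted. Causality is left to the health care provider.
- **Laxative use.** "All participants will be asked to discontinue laxative use at the first intervention visit and to refrain from using laxatives throughout the trial". The section describes this "as is standard UK practice in specialist biofeedback services".
- **Table 1 (habit training), item c.** "Advice to stop all laxatives including drugs which have a laxative effect", with irrigation devices and enemas also ruled out. The same item says that one or two "glycerin suppositories are permitted as rescue if no stool is passed for 3 days".
- **Exclusion criteria.** Rectal impaction at entry is an exclusion.

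**The concern.** The exemption treats an admission for constipation as background illness. In this trial it may not be. Participants have failed at least two laxatives or prokinetics, are then asked to stop laxatives as part of the intervention, and are free of impaction when they enter. Admission for worse constipation or new impaction is therefore a plausible serious consequence of a trial procedure.

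The rule looks only at the type of event and not at its cause. A site that judged such an admission to be caused by trial procedures would still be told not to report it.

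The value of the safety record is at stake. The Criteria for discontinuation section lets the DMEC, the steering committee, the ethics committee or the sponsor end the trial on safety grounds. It defines no stopping criteria, and the Trial committees section plans no interim analysis. Those bodies therefore depend on what reaches them.

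**Working it through.** The plan gives no figure on this point, so the check is mainly a comparison of sections.

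**1. Does laxative withdrawal apply to everyone?** Yes. Table 1 makes it part of habit training. The Group 2 section says that HTBF sessions contain every feature of habit training. Group 3 participants receive one or the other. The Laxative use section says the same for all participants. The number affected is the full sample, 147 + 147 + 100 = 394.

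**2. Would impaction be a new event?** Yes, because it is excluded at entry.

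**3. Does the exemption depend on relatedness?** No. The second listed item shows that the authors could add such a qualifier. The constipation item has none.

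**4. What does the exemption remove?** The text allows two readings.

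| Reading | Consequence for an admission judged related |
|---|---|
| The list only defines which SAEs count as expected for the 24-hour and 15-day route | It does not take that route. It stays on the case report form. The article does not say how it is reported after that. |
| The list removes these events from SAE reporting altogether | It is recorded but not reported, against the stated purpose of the recording |

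The position of the list, directly after the expedited rule, favours the first reading. The unqualified wording favours the second. So does the second listed item: unrelated events are already outside a route reserved for related and unexpected ones, so they would not need an exemption from it. The text does not settle the matter.

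**5. Where else could these admissions appear?**
- The case report form (Harms).
- Review of related adverse events at each intervention visit and at follow-up (Study visits).
- NHS resource use and the patient journal's record of health contacts (Secondary clinical endpoints).
- The study data that are quality-checked before the data monitoring committee sees them (Data management).

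None of these sections says that the exempted admissions are counted for the committee.

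**6. Could such events occur at all?** The documents give no admission rate, so the rates *p* below are assumptions. Expected number = 394 × *p*. Probability of at least one = 1 − (1 − *p*)^394.

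| Assumed *p* | Expected admissions | Probability of at least one |
|---|---|---|
| 0.25% | 1.0 | 63% |
| 0.5% | 2.0 | 86% |
| 1% | 3.9 | 98% |
| 2% | 7.9 | nearly 100% |

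Over this range, an event that is rare for each participant would still probably occur somewhere in the trial.

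**The case against.** The strongest reply is that not reported does not mean not seen. The list follows the expedited rule, and exempting listed expected events from expedited reporting is common. SAEs go on the case report form without exception, and study data go to the data monitoring committee. Resource use, which would include such an admission, is compared between arms in the economic analysis. This stands. A reader might infer that these admissions are kept from the sponsor and the DMEC altogether, but no section says so.

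The other points of the reply, and what remains of each:

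- **Withdrawal is described as standard practice, a rescue is defined, and telephone support is offered between visits.** These may lower the rate. They are no reason for leaving out an event judged related. It also follows that the documents do not support calling this the most foreseeable serious harm, since they rank no harms.
- **All arms stop laxatives.** This stands. A comparison by arm cannot isolate the effect of withdrawal, because no arm continues laxatives.
- **Expected is the counterpart of unexpected in the preceding rule.** This is fair. The rarity of the event does not by itself show that the exemption is wrong.
- **The advice to see the family physician "for any unrelated signs, symptoms or disease or aggravation of underlying symptoms" concerns where participants seek care.** This is correct. It is not a rule on recording or reporting, and the point does not rest on it.
- **A zero count in the final report would mislead.** Nothing says that the final report omits SAEs held on the case report form, so an upper limit such as 3/394 (about 0.8%) drawn from an artificial zero is speculation.
- **A journal article condenses the full protocol.** This would answer an omission. The point here is a rule that the article states.

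**Conclusion.** The point holds in a limited form. The Harms section exempts a class of SAE from reporting by event type alone. Trial procedures could plausibly cause that class, and the exemption applies even when a site judges the event related. It also sits badly with the same section's reason for recording SAEs.

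It is not shown that the events are invisible to oversight. They remain on the case report form and may reach the DMEC with the study data. The size cannot be stated from the documents. About 1 to 8 admissions among 394 participants is an illustration that rests wholly on the assumed 0.25% to 2%.

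Since laxatives are stopped in every arm, the overall count and the causality judgement in each case carry most of the information. Counts by arm are still worth having, because the arms differ in other respects. The change is worth making because it protects the safety record at very little cost.

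**What to change.** Reconcile the two statements in the Harms section:

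1. Limit the exemption for constipation and impaction admissions either to expedited reporting (the 24-hour and 15-day route) or to events judged unrelated to trial procedures, and say which.
2. State that these admissions are still recorded on the case report form, with a causality assessment that considers trial procedures, including laxative withdrawal.
3. Summarise them overall and by randomised arm for the DMEC and in the final report.

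The exemption for unrelated elective surgery and accidental injury can stay. No change to the laxative or rescue rules is proposed.

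The cost is a protocol wording change, a few more forms for sites and sponsor, and one further line in the safety tables.
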